**Fig. 2 Fig2:**
[figure not shown]
Sequential testing safety profile. The plot is based on a likely sample size of 75 patients per treatment strategy, a 1-sided α = 0.05, an expected seizure recurrence rate ≤ 30 % and a cut-off point for safety, which is a recurrence rate of ≥ 40 %. The red boundary represents the safety margin. The following formulas will be used to plot data in the graph: *Ζ* = −(*F* − *n* × *Pc*) (→*Ζ* = number of observed seizure recurrences – number of expected seizure recurrences), *V* = *n* × *Pc* (1 − *Pc*) (→*V* is the variance of *Z* and stands for the amount of information in *n* patients, with *n* being the number of included patients, *Pc* the expected seizure recurrence risk (i.e., for the selected patient cohort: 0.30) and *F* the number of observed seizure recurrences). The vertical line is the anticipated value for *V* for a sample size of 75 patients

### Adverse event reporting

For this study, recurrent epileptic seizures during AED withdrawal that need hospitalization do not necessarily have to be recorded as serious adverse events (SAEs), but are noted in the case report form (CRF) as one of the outcome measures, and will be included in the interim safety analyses by the DSMB. Epileptic seizures that lead to a potentially life-threatening situation, such as status epilepticus, will be reported as SAEs.

All SAEs will be reported through the web portal “ToetsingOnline,” to the accredited ethical committee that approved the protocol, within 15 days after the sponsor has first knowledge of the serious adverse reactions. Participating centers will inform the sponsor about the SAEs. Reporting of SAEs that result in death or are life-threatening should be expedited. The expedited reporting will occur not later than 7 days after the responsible investigator has first knowledge of the adverse reaction. This is for a preliminary report with another 8 days for completion of the report.

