## Methods/Design

### Study design

The TimeToStop trial will be a European multicenter pragmatic randomized clinical trial. In the Netherlands the trial has been approved by the Medical Ethical Committee of the University Medical Center Utrecht, which is the leading ethical committee. Other participating centers are in the process of protocol submission and have not yet obtained definite approval. Only then, local patient recruitment will start. For every patient who will be included in the trial we will obtain informed consent. In the TimeToStop trial, index intervention is early withdrawal: AED withdrawal is started 4 months after surgery and completed within 8 months after start of withdrawal (thus, at latest 12 months postoperatively). Reference intervention is late AED withdrawal: tapering off medication starts at 12 months after surgery and completion should be within 20 months after surgery. For both treatment arms, the total tapering period is set at 8 months maximum and clinicians may decide which AED they want to taper first and at what speed they will reduce each individual drug. A tapering period of 8 months is considered reasonable, as from the retrospective TimeToStop (TTS) study [16] it could be calculated that patients who fulfill the inclusion criteria used on average 1.7 AEDs prior to surgery (range 0–3). The late (reference) starting point of AED tapering – i.e. 12 months – is based on current practice; the median interval between surgery and drug reduction in our retrospective European study was 12.5 months [16]. The 4 months’ time-point in the early withdrawal group is selected mainly because of logistical reasons. First, informing parents and recruiting patients needs time. Second, inclusion requires proof of early surgical success, which needs a certain time window to discriminate between acute postoperative (running-down) seizures and true seizure recurrence. Third, in some children clinicians may want to prove completeness of resection by performing a postoperative magnetic resonance imaging (MRI), for which a minimum follow-up time of a few months is required. For both intervention strategies, the treating physician is allowed to start tapering earlier if patients experience unacceptable side effects of prescribed AEDs. Rescue medication that is started preoperatively and withdrawn shortly after surgery, can be discontinued according to existing local routine practice, and will not be investigated in this study.

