#### Outcome parameters

Cognitive outcome: differences in EpiTrack scores, IQ scores and other continuous outcome measures of neuropsychological assessment will be analyzed using independent samples *t*-tests or other tests depending on distributions. EpiTrack and IQ differences will be assessed cross-sectionally to answer the primary research question. Additionally, longitudinal changes in EpiTrack measures and IQ compared to preoperatively will be assessed between both treatment arms using linear mixed models. We will calculate a number needed to treat, expressed as the number of patients required to taper drugs earlier to achieve one more patient with improvement in attention. Analyses will be considered statistically significant if 95 % confidence intervals for group differences do not include 0, compatible with a 2-sided *p* < 0.05. For chances of eventual seizure freedom and “seizure and AED freedom”; we will calculate a relative risk and a risk difference with 95 % confidence intervals. Chances of eventual seizure freedom and “seizure and AED freedom” will be compared between the groups at 24 months after surgery and at 20 months following start of AED withdrawal; for the early withdrawal arm this will be at 24 months and for the late withdrawal arm at 32 months.

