With regard to safety; due to the design of the trial, an interim safety analysis comparing both treatment arms at one moment is not possible. This is because we expect in both arms relapse risks to increase particularly once AED withdrawal is started. Thus, in the early withdrawal group recurrences probably occur sooner than in the late withdrawal group, although the total risk of relapse at the end of follow-up is not expected to differ between groups. This implies that at interim time points, when inherently more patients are under AED reduction (at increased risk of relapse) in the early arm, a fair comparison of relapse between both groups is not feasible. To deal with this, we will assess safety in each arm separately. The study intervention will be considered safe when seizure recurrences occur in less than 40 % of both treatment arms. This percentage is chosen based on the general seizure freedom rate after childhood epilepsy surgery of 41 to 93 % [1, 2]. Based on previous identification of risk factors for seizure recurrences, we expect recurrence rates in the patients included in the trial to be < 30 %, due to exclusion of patients with identified risk factors [1, 16, 22, 23]. We do not expect, however, the seizure status to be better than in normal clinical practice. Because of the expected cognitive benefit due to a longer AED-free period, a 40 % rate of seizure relapse will still be accepted. The DSMB statistician will analyze the number of patients with seizure recurrences every 3 months during trial duration, in order to allow early awareness of unexpected high numbers of recurrences, exceeding the 40 % limit. In this sequential testing safety model (Fig. 2), a 1-sided *p* value < 0.05 will be considered significant for the safety monitoring [24, 25].

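### The SAE exemption for hospitalised, non-life-threatening seizures is tied to the taper phase, so whether an admission is recorded as an SAE at a given time since surgery depends on the arm

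*Protocol article*

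**What the plan says.** The adverse event reporting section of the protocol article sets the rule: "recurrent epileptic seizures during AED withdrawal that need hospitalization do not necessarily have to be recorded as serious adverse events (SAEs"). The exempt events are not lost. They "are noted in the case report form (CRF) as one of the outcome measures, and will be included in the interim safety analyses by the" monitoring board (DSMB). The most severe seizures stay outside the exemption: "Epileptic seizures that lead to a potentially life-threatening situation, such as status epilepticus, will be reported as SAEs". SAEs go to the ethics committee that approved the protocol.

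The study design section fixes when withdrawal takes place. In the early arm, "AED withdrawal is started 4 months after surgery and completed within 8 months after start of withdrawal (thus, at latest 12 months postoperatively"). In the late arm, "tapering off medication starts at 12 months after surgery and completion should be within 20 months after surgery".

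The safety monitoring section says that the DSMB statistician "will analyze the number of patients with seizure recurrences every 3 months during trial duration", with safety assessed within each arm separately. Under outcome parameters, seizure freedom is compared at 24 months after surgery and at 20 months after the start of withdrawal; for the latter, "for the early withdrawal arm this will be at 24 months and for the late withdrawal arm at 32 months".

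**The concern.** An SAE rule should give the same label to the same event whichever arm the child is in. Here the label depends on whether the child is tapering, and the calendar time of tapering is exactly what is randomised. A child admitted with a non-life-threatening seizure at month 8 falls under the exemption if allocated to early withdrawal, but not if allocated to late withdrawal. At month 16 it is the other way round.

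Two features add to this. First, the wording permits but does not require omission, so an exempt admission may be an SAE at one site and not at another. Treating physicians know the allocation, and the discussion section describes regional preferences about withdrawal timing. Second, the stated reason for the exemption is that these seizures are already outcome data. That reason applies equally to recurrences before tapering starts and after it ends, yet the exemption is not extended to them.

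At stake is how a listing of SAEs by arm, or the stream of reports to the ethics committee, is read in a trial whose second hypothesis is that early withdrawal is safe.

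**Working it through.** **Inputs** (protocol article)
- Early-arm withdrawal: starts at month 4, lasts at most 8 months (study design).
- Late-arm withdrawal: starts at month 12, lasts at most 8 months (study design).
- Seizure outcome: month 24, and 20 months after the start of withdrawal (outcome parameters).
- Exemption: applies during withdrawal only (adverse event reporting).

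**Assumptions.** Randomisation is at about month 4, every taper is on schedule and every taper uses the full 8 months.

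**The plan's own dates reproduce.** End of taper: 4 + 8 = 12 and 12 + 8 = 20. Second seizure assessment: 4 + 20 = 24 and 12 + 20 = 32.

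**Overlap of the exempt windows.** The early window ends at month 12, when the late window starts. Overlap: 12 − 12 = 0 months.

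**Counted by time since surgery**

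| Months after surgery | Early arm | Late arm |
|---|---|---|
| 4 to 12 | 8 exempt | 8 not exempt (before taper) |
| 12 to 20 | 8 not exempt (after taper) | 8 exempt |
| 20 to 24 | 4 not exempt (after taper) | 4 not exempt (after taper) |
| Total, 4 to 24 | 8 exempt, 8 + 4 = 12 not | 8 exempt, 8 + 4 = 12 not |

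The totals to month 24 agree, but the stages do not. The early arm's 12 non-exempt months all follow withdrawal. The late arm's are 8 months before tapering and 4 months after it.

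**Counted from the start of withdrawal, over 20 months.** Early arm (months 4 to 24): 8 exempt, then 12 not. Late arm (months 12 to 32): 8 exempt, then 12 not. On this clock the rule is the same in both arms. The late arm has a further 8 non-exempt months before its clock starts.

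**Events affected.** Only hospitalised, non-life-threatening seizure recurrences. The documents give no rate for these, so the number of SAEs concerned cannot be calculated.

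**The case against.** The strongest reply is that no planned analysis uses the label. The protocol plans no between-arm comparison of SAE counts. Safety monitoring rests on seizure recurrences within each arm, and the efficacy-side seizure comparisons rest on seizure freedom and on seizure and drug freedom. The safety monitoring section itself says that comparing relapse between arms at interim time points is not fair. All of this stands, and it is why the point is minor.

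A reader might go further than the text allows in several ways:

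- *That SAE counts cannot be compared at all.* Other SAEs and life-threatening seizures follow one rule in both arms throughout, and counts aligned to the start of withdrawal fall under one nominal rule.
- *That relapse severity cannot be reported by arm without bias.* Exempt admissions are noted in the CRF and non-exempt ones are SAEs, so a count by arm can be rebuilt if hospitalisation is recorded for each recurrence. The CRF is not shown.
- *That the DSMB will not see hospitalised seizures by arm.* The protocol says that these events enter the interim safety analyses and that the committee works on unblinded data. The sequential test on recurrences need not be all it receives.
- *That monitoring gives an admission the same weight as an aura.* Auras appear in the definition of seizure freedom; the safety monitoring section does not define recurrence that way.
- *That the rule favours early withdrawal overall.* That direction is confined to the period up to month 12 and then reverses.

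The reply does not remove the rule itself. As written, recording at a given time since surgery depends on the arm, and the discretion makes it depend on the site as well.

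**Conclusion.** The point holds in a limited form and is minor. Raw counts of hospitalised-seizure SAEs by arm, taken by time since surgery or from randomisation, combine how often admissions occur with which arm is exempt at that time. On schedule, the exemption covers all 8 months from month 4 to month 12 in the early arm and none in the late arm; from month 12 to month 20 the reverse holds. The same applies to what the ethics committee receives.

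The month counts rest on full 8-month tapers, on schedule. Actual windows will vary: 8 months is a maximum, clinicians choose the speed, tapering may start earlier for unacceptable side effects, and patients may restart drugs after a recurrence. The text does not say whether a child who has restarted still counts as being in withdrawal. This variation blurs the boundary but does not make the rule independent of the arm.

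No estimate, monitoring boundary or sample size in the protocol changes.

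**What to change.** State one SAE recording rule for all hospitalised seizure recurrences, in both arms, from randomisation to the end of follow-up, whatever the taper phase. Two versions would work: all are SAEs, or all are recorded as outcomes only, with life-threatening seizures remaining SAEs. Remove the discretionary wording in either case. Make sure the CRF records hospitalisation for each recurrence, and report hospitalised recurrences by arm from the CRF alongside the SAEs.

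The cost is a wording change, a CRF field if one does not already exist, and one extra line in the safety report. If all hospitalised recurrences become SAEs, sites have slightly more to report. The article states that no patient had yet been included, so at that stage no recorded data would need to be reclassified.

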## Discussion

We present the protocol of a European pragmatic randomized clinical trial, designed to investigate the possible benefits and the safety of early AED withdrawal after epilepsy surgery in children. We hypothesize that early AED withdrawal is safe, in terms of seizure relapse rates and eventual seizure outcomes, and will improve cognitive functioning, behavior and quality of life, compared to late withdrawal. We will investigate these hypotheses by randomly allocating patients to an early withdrawal group that starts withdrawal of medication 4 months after surgery, versus a late withdrawal group, that starts withdrawal of medication after 12 months. Justification of this trial needs to be discussed. The non-experimental evidence obtained so far on safety of AED withdrawal in relation to seizure outcome seems strong and consistent [16, 17]. In analyses that had been elaborately adjusted for confounding, there was a slightly increased recurrence risk for earlier withdrawal, but not for regain of seizure freedom rates and eventual seizure outcome. Moreover, findings on cognitive outcome after AED withdrawal all pointed towards cognitive improvement on several domains [3–15]. Why then do we think that the trial will have important added value? Through randomized allocation the study population will be broader than in the non-experimental studies which only pertained to patients for whom AED withdrawal had already been decided about. Consequently, results will have wider clinical applicability and will apply to all patients who are eligible for withdrawal decision- making. A very important asset will be obtaining baseline comparability of treatment arms for both known and measurable confounders, but also for unknown or unmeasurable confounders. In principle, the non-experimental evidence, although elaborately adjusted for known confounders, does leave residual confounding as an explanation. The trial will allow for full follow-up of all children randomized and for intention-to-treat analysis. Finally, through the above, stronger evidence will contribute to our ultimate goal, implementation of evidence-based practice concerning AED withdrawal. Although previous non-experimental research does seem to indicate benefits of early AED withdrawal, it is especially the remaining uncertainty about residual confounding that leads us to claim that there currently is genuine equipoise about timing of withdrawal and, therefore, that random allocation is ethically justified. This issue will have to be addressed with regard to trial feasibility. Throughout European centers participating in the trial, there are regional preferences concerning AED withdrawal timing, and non-experimental evidence has already led to changes in clinical practice concerning withdrawal timing. It will be vital for successful completion of the trial that participating physicians can and will be convinced that there still is true equipoise, as a sufficient basis for studying randomized AED withdrawal timing to the ultimate benefit of children who have undergone epilepsy surgery.

Recruitment of participants for this study might be challenging for three reasons. First, in some of the participating countries and centers, AED withdrawal policies are still rather conservative, conflicting with the proposed early AED strategy. This may either be due to reluctance of parents or patients to risk a seizure relapse, now that seizure freedom has finally been achieved following epilepsy surgery, or to fear of the treating neurologist or neurosurgeon that seizure control is permanently lost after a post-withdrawal relapse. In addition, in some patients treating physicians may require a postoperative MRI to prove complete resection of the epileptogenic lesion before considering AED withdrawal. Planning of MRI scanning before randomization may not always be feasible in the proposed short time period. Second, in many participating centers, AED withdrawal policies already tend to change towards earlier reduction, as a consequence of the findings from the previous retrospective observational TTS study [16]. These changing opinions on AED withdrawal policies are not only known among physicians, there is also an increasing awareness of safety of early withdrawal among parents of children who have been operated on. Therefore, willingness to be randomized to the late withdrawal strategy arm may prove difficult in these centers. Third, some treating physicians may not want to withdraw AEDs within a set maximum time frame of 8 months, or only consider reduction of medication instead of complete discontinuation of AEDs, fearing that relatively early, rapid or complete withdrawal may increase the risk of seizure relapse. To prevent limited recruitment of patients we will encourage participating physicians to counsel parents and patients optimally, based on the available evidence regarding safety of AED withdrawal, which can be summarized as follows: although retrospective data suggest that early withdrawal is safe and does not compromise eventual seizure outcome or treatability of seizure relapse, definite proof of safety in a predefined population of children who underwent anticipated curative surgery is still required, justifying randomization to either treatment arm. Furthermore, although we anticipate cognitive improvement following AED discontinuation, the – possibly enduring – cognitive advantages of early over late withdrawal need to established, which is important to enable careful balancing of risks and benefits of early AED discontinuation in individual patients in the future.

### Data Safety Monitoring Board

The DMSC analyses the unblinded data on a permanent basis and formulates recommendations for the Steering Committee on the continuation of the trial. The Data Monitoring Committee may also offer unsolicited recommendations. Members of the Data Monitoring Committee are: [name]. [name], child neurologist, epileptologist, UMCG; [name] [name], statistician, UMCU; [name]. [name], neurologist, UMCU.

## Trial status

Ethical approval has been obtained for the University Medical Center Utrecht. The other participating centers are in the process of obtaining approval. No patients have yet been included in the trial.

## Abbreviations

AED: antiepileptic drug
CBCL: Child Behavior Checklist
CI: confidence interval
CRF: case report form
DSMB: Data Safety Monitoring Board
EEG: electroencephalogram
HASES: The Hague Side Effects Scale
HR: hazard ratio
IQ: Intelligence Quotient
MRI: magnetic resonance imaging
PedsQL^TM^: Paediatric Quality of Life Inventory^TM^
SD: standard deviation
PIQ: Performal IQ
SAE: severe adverse event
SD: standard deviation
TTS: TimeToStop
VIQ: Verbal IQ
